### Prolonged QTc

Prolongation of the QT interval will be actively monitored with daily pre and 2 hour post Tamoxifen dose 12 lead ECGs at 50mm/s for the first 2 weeks of treatment, and weekly after that, unless they are indicated more frequently. Trained study staff will measure and calculate the corrected QT interval. It is expected that around 10–50% of patients will develop prolonged QTc intervals while on treatment
^13,
16^. With some drugs, a prolonged QTc can lead to a polymorphic ventricular tachyarrhythmia (Torsades de Pointes, TdP) which can be life threatening. However, this has not been described in patients receiving Tamoxifen, including in those receiving higher doses as will be used in this study
^12,
13,
16,
26^. Prolongation of the QT interval has also been reported in patients receiving fluconazole, but TdP has only rarely been described with less than 10 reports published at the time of writing, despite its extensive use
^38,
40^. Moreover, in a case series of cancer patients receiving fluoroquinolones (which also prolong the QT interval) combined with fluconazole, despite QT prolongation there were no episodes of arrhythmias
^42^. In this study QT prolongation will be managed in line with American Heart Association guidelines as described below
^32^. Any risk of TdP will be mitigated by close monitoring and management of electrolytes, particularly potassium, calcium and magnesium. The use of other drugs which can prolong the QTc and have been associated with TdP, other than fluconazole, will be prohibited during the first 14 days following randomization. Appendix 4 of Extended data
^58^ lists such drugs.

If the QTc is >500ms,

1. Do not administer further tamoxifen until the QTc is ≤ 500ms.2. Immediately recheck blood potassium, calcium and magnesium levels.3. Complete a Cardiac Adverse Event form from the CRF4. Correct abnormal electrolytes into the mid normal range with intravenous supplementation (potassium chloride, calcium gluconate or chloride, and magnesium sulfate). Use intravenous access separate to the amphotericin infusion when administering electrolytes.5. Repeat the ECG, a 30 second rhythm strip, and serum electrolytes 2 hours prior to the next due dose of Tamoxifen.a) If the QTc is >500ms, the due dose of tamoxifen should be omitted.b) If the QTc is ≤500ms but there are extra-systoles, the next dose of tamoxifen should be omittedc) If the QTc is ≤500ms and there are grade 2 or greater abnormalities in serum potassium, magnesium or calcium levels, the next dose of tamoxifen should be omitted.d)If the QTc is ≤500ms, and there are no extra-sytoles, and the calcium, potassium and magnesium levels are normal or no more than grade 1 abnormal, the next due dose of tamoxifen can be given.6. Where the QTC is >500msec, the administration of tamoxifen is suspended and the patient musta)have daily ECGs and monitoring and correction of electrolytes until the QTc is less than 500ms.b)When the QTc is <500ms, Tamoxifen can be restarted according to the guidance in 5 a-d above.7. Tamoxifen is administered until day 15 after randomization. All due, received and missed drug doses must be recorded in the study case record form (CRF).8. Any patient where the QTc is greater than 500ms AND is accompanied by syncope OR arrhythmia should have review by a cardiologist.

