### Pharmacology and dosing

Tamoxifen has excellent dose-independent oral bioavailability (approximately 100%) with minimal first-pass metabolism
^24^. The half-life is 5–7 days. Tamoxifen’s SERM activity requires serum concentrations ~100 ng/mL. This is achieved with doses of 20 – 60 mg/day, and for breast cancer treatment at this dose is recommended for 5–10 years
^25^. At these doses, brain tissue concentrations are 40-100-fold higher (4-10 µg/mL), than in serum
^23^. Higher doses of 240 – 500mg/day have been studied in clinical trials of treatment for CNS tumours, desmoid tumours and lung cancer and are well tolerated, safely achieving serum concentrations of 2-8ug/mL
^12–
14,
26–
28^. Treatment administration regimens at these doses vary: month-long cycles of 300mg/day are given for desmoid tumours in children
^28^; doses of 120mg/m
^2^ BID have been given for up to 1 year and well tolerated in patients with glioblastoma multiforme
^27^. Such treatment regimens establish Tamoxifen serum concentrations around the
*C. neoformans* MIC and, will achieve brain concentrations 40-100-fold higher, suggesting levels sufficient to treat CM will be achieved using oral dosing in humans
^23^. Moreover, uniquely compared with other antifungal drugs, Tamoxifen is further concentrated in macrophage phagosomes – an important site of
*C. neoformans* replication
^11^.

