### Intervention arm: Induction phase treatment (days 1–14)

Tamoxifen will be given orally in a dose of 300mg/day for the first 14 days following randomization. It will be administered by nasogastric tube where patients are unconscious. In addition patients will receive amphotericin 1mg/kg once daily i.v. and fluconazole 800mg once daily orally. The Tamoxifen will be administered in the morning combined with amphotericin and fluconazole dose.

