### Continuation phase of treatment (days 15–70)

After the first 2 weeks of study treatment, all patients will receive fluconazole 800mg/day for 8 further weeks, until the study end. At this point, HIV infected patients will be switched to long term secondary prophylaxis with fluconazole 200mg/day as per standard practice. For HIV uninfected patients, the decision to continue antifungal treatment, and at which dose, will be made on a case by case basis by the attending physician in consultation with the patient.

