## Patient management

### Initial evaluation

On admission all patients will have a full clinical assessment and examination.

Study entry laboratory tests will be performed as per the study schedule in
Table 2.

**Table 2. T2:** Trial Assessment and Investigation Schedule
*.

Action	Day 1(study Entry)	Day 3	Day 5	Day 7	Day 9	Day 11	Day 14	Day 21	Day28	Day 42	Day 70
**Take informed consent**	X										
**Clinical Assessment ****	X	X		X		X	X	X	X	X	X
**Full blood count**	X			X							X
**Sodium, Urea, Creatinine,** **Glucose**	X	X		X		X	X	X	X	X	X
**Magnesium and Calcium**	X	X	X	X	X	X	X	X			
**ALT and AST**	X			X			X				
**Potassium**	Daily for first 14 days							X	X		
**CD4 count**	In first week										X
**HIV test**	X										
**Blood cultures**	X										
**Cerebrospinal fluid (CSF)** **opening pressure**	X	X		X			X	if clinically indicated			
**Cryptococcal Lateral flow** **antigen test (CSF)**	X										
**CSF Gram's stain, India ink**	X	X		X			X				
**CSF cell count, protein,** **glucose**	X	X		X			X				
**CSF TB smear/geneXpert**	During first week										
**CSF Yeast quantitative** **culture**	X	X		X			X				
**Store *C. neoformans*** **isolate**	X	X		X			X				
**CSF for Pharmacokinetics**	X	X		X							
**Plasma for** **pharmacokinetics**	X			X							
**Sputum TB smear *****	X										
**Electrocardiogram**	Twice daily for first 14 days										
**Chest X-ray**	X										
**Approximate total blood** **volume mL**	21.5										
**Approximate total CSF** **volume mL**	up to 25	up to 25		up to 25			up to 25	up to 25	up to 25	up to 25	up to 25

* Study drug is given daily from day 1 – day 14** GCS Assessment is daily while an in-patient. When outpatient, assessment can take place at the scheduled time + up to 5 days (e.g. 4 week assessment on day 28-33). ***at doctor’s discretion **** volume determined by CSF pressure N.B.: Blood volumes are estimates

**Table 3. T3:** simple visual assessment.

Record the best performance of each eye	
Function	Score
Normal	1
Blurred	2
Finger counting	3
Movement perception	4
Light perception	5
No light perception	6

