### Cardiac monitoring

ECGs (50mm/sec) will be performed twice daily immediately before and 2 hours after administration of Tamoxifen during the first 14 days, and on days 21 and 28. ECGs can be repeated more frequently according to the patient’s needs. The QTc will be calculated as described in section ’Prolongation of the QT Interval’.

*Laboratory monitoring*

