Appendix 1 - Management of raised intracranial pressure

Appendix 2 - Amphotericin administration and complications

Appendix 3 - Presumptive and definitive criteria for AIDS defining events

Appendix 4 - Drugs associated with prolonged QTc and TdP which must not be coadministered with Tamoxifen during the first 2 weeks of this study.

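### The ban on other QT-prolonging drugs ends on day 14 with the last tamoxifen dose, without a washout, and starting such a drug afterwards triggers no ECG or electrolyte check

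*Protocol article*

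**What the plan says.** **The ban.** The Prolonged QTc section says that the use of other QTc-prolonging drugs associated with torsades de pointes (TdP), fluconazole excepted, "will be prohibited during the first 14 days following randomization". The title of Appendix 4 in the Extended data list sets the same limit: it covers drugs "which must not be coadministered with Tamoxifen during the first 2 weeks of this study".

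**Tamoxifen.** The dose is "300mg/day for the first 14 days following randomization", and the Table 2 footnote agrees: "Study drug is given daily from day 1 – day 14". Pharmacology and dosing states: "The half-life is 5–7 days".

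**Fluconazole.** It also prolongs the QT interval and does not stop: "all patients will receive fluconazole 800mg/day for 8 further weeks".

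**Monitoring after day 14.** Cardiac monitoring schedules ECGs "during the first 14 days, and on days 21 and 28". Prolonged QTc describes pre-dose and post-dose ECGs "for the first 2 weeks of treatment, and weekly after that, unless they are indicated more frequently". Table 2 marks potassium, magnesium and calcium on day 21 and potassium on day 28. The Blood section instead leaves levels after the first two weeks to clinical need.

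**New drugs.** The section on concomitant medications has them recorded at each visit. It attaches no ECG or electrolyte action to a new start.

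**The concern.** The ban limits the number of QT-prolonging drugs acting at once. Its end date follows the dosing calendar, but a drug with a half-life of 5–7 days is still present well after its last dose. The restriction is therefore lifted when tamoxifen is near its highest level of the course.

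At the same point ECGs go from twice daily to roughly weekly, and daily potassium measurement stops. A clinician may then start a third QT-prolonging drug, such as a fluoroquinolone, and the plan requires no ECG or electrolyte measurement in response.

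What is at stake is patient safety in a short window. The Risks section says it is unclear whether tamoxifen plus fluconazole raises the risk of QT prolongation and TdP, and the sponsor judged a third drug worth banning during dosing.

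**Working it through.** The plan gives no figure of its own on this point, so there is nothing to reproduce. The check sets the ban's end date against the protocol's half-life.

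**Inputs from the protocol.** Fourteen equal daily doses, days 1–14; half-life t of 5 to 7 days; ban ends on day 14; next scheduled ECG on day 21.

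**Assumptions.** One compartment, first-order elimination, parent drug only, no missed doses.

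**Level after the last dose, in first-dose units.** With r = 2^(−1/t), A = (1 − r^14)/(1 − r).
- t = 5: r = 0.871, A = (1 − 0.144)/(1 − 0.871) = 6.62 (unrounded r)
- t = 7: r = 0.906, A = (1 − 0.250)/(1 − 0.906) = 7.96 (unrounded r)

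This is the highest level of the course. It is 86% of steady state at t = 5 and 75% at t = 7.

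**Share of that peak remaining on day d**, 2^(−(d − 14)/t):

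| Day | t = 5 | t = 7 |
|---|---|---|
| 15 (ban off) | 87% | 91% |
| 17 | 66% | 74% |
| 20 | 44% | 55% |
| 21 (next scheduled ECG) | 38% | 50% |
| 28 (following ECG) | 14% | 25% |

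**Share of total course exposure between day 15 and day 21.** A(r − r^7)/14 = 6.62 × (0.871 − 0.379)/14 = 23% at t = 5, and 7.96 × (0.906 − 0.500)/14 = 23% at t = 7.

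**Length of the unmonitored interval.** From a start on day 15 to the next mandated check on day 21 is 21 − 15 = 6 days. If the Blood section's wording overrides Table 2, no electrolyte check is mandated on day 21 either.

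**Sensitivity to missed doses.** If doses 8–10 are withheld, day 15 loses r^5 + r^6 + r^7 first-dose units: 1.31/6.62 = 20 points at t = 5 and 1.66/7.96 = 21 points at t = 7. That leaves 67% and 70% of the full-dose peak. If dosing stops after day 7, the day-14 level is only 27% and 33% of that peak, and the point is much weaker.

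**The case against.** The case for leaving the rule alone has substance.

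- **A day-15 start follows a recent check.** The patient has had pre-dose and post-dose ECGs for 14 days, daily potassium, and magnesium and calcium on day 14. Tamoxifen only falls from there. This stands: what is missing is a check after the start, and a check before later starts.
- **Patients already shown to be at risk stay covered.** While QTc exceeds 500 ms, daily ECGs and electrolyte monitoring and correction continue. Baseline QTc above 500 ms, known conduction defects and existing QT-prolonging medication are exclusions. This also stands, so only new starts in patients with acceptable QTc matter.
- **Extra ECGs are allowed, and amphotericin, the usual cause of electrolyte disturbance, ends with induction.** Both are true, but a permitted ECG is not a required one.
- **The expected risk is low.** The protocol reports no TdP described with tamoxifen, few reports with fluconazole, and no arrhythmias in a series combining fluoroquinolones with fluconazole. That limits the weight of the point without explaining why the ban ends where it does.
- **An operational trigger may sit in the full protocol.** That is possible, but the article does fix the end date, and the end date is what clashes with the half-life.

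A reader might go further and infer that cardiac monitoring lapses after day 14. The scheduled checks on days 21 and 28 contradict that.

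A reader might also infer that the ban ends before dosing does, because item 7 of the QTc rules runs tamoxifen until day 15. That wording can be read as excluding day 15, and two other places give day 14, so it is a clerical matter.

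Finally, the first-dose level is 1/A, or 15% and 13% of peak. A reader might conclude that the sponsor considers so low a level hazardous because the ban applies from day 1. It does not follow: a drug started on day 1 would meet accumulating tamoxifen and amphotericin.

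**Conclusion.** The point holds as a minor safety improvement. The ban's end is set by the dosing days and not by the protocol's own half-life. At day 15 about 87–91% of the course-peak tamoxifen level remains, with fluconazole continuing at full dose. A newly started QT-prolonging drug can run about 6 days before a mandated ECG or electrolyte check.

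The percentages rest on one-compartment kinetics, full dosing and the stated 5–7 day half-life. They describe exposure, not harm. The document gives no relation between concentration and QTc and no frequency of such co-medication, so an excess risk of arrhythmia cannot be calculated and none is claimed. The fungal-clearance primary endpoint is not affected, and nothing here shows bias in the QTc comparisons.

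**What to change.** Add two sentences to the Prolonged QTc section and align the Appendix 4 title:

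- From day 15 to at least day 28, avoid Appendix 4 drugs where an alternative exists.
- If one is needed, obtain an ECG and potassium, magnesium and calcium before starting it (day-14 results suffice for a day-15 start) and again shortly after.

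Day 28 leaves 14–25% of the peak level. It is a practical choice and not a derived threshold, and a later date is defensible at the 7-day half-life. The rule is needed at minimum in the tamoxifen arm. Applying it to both arms keeps the planned QTc comparison after day 14 balanced, but restricts control patients who carry no tamoxifen. Separately, reword item 7 of the QTc rules so that the last dose is clearly on day 14.

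The cost is a mild two-week restriction on co-medication and a few extra ECGs and blood tests. Because the rule is to avoid or monitor, needed treatment is not blocked. The article reports that enrolment has finished, so the practical use is in reviewing co-medication started after day 14 and in designing the larger trial.

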### Ventricular tachyarrhythmia

In the event of TdP or any other ventricular tachyarrhythmia, patients will receive oxygen and be transferred to a high care environment for continuous cardiac monitoring. If there is cardiovascular compromise, resuscitation will follow normal practice. Electrolytes will be rechecked, corrected if needed, and administration of Tamoxifen and fluconazole suspended.

TdP usually occurs in unsustained bursts that spontaneously terminate. However,
**the specific treatment of TdP is intravenous magnesium**, given as Magnesium sulfate in a dose of 1–2 g intravenously over 5 to 10 minutes diluted in 50–100mls of 5% dextrose. This can be repeated in 5–15 minutes. Alternatively, a continuous infusion can be started at a rate of 3–10 mg/min. Note: Magnesium is effective even in patients with normal magnesium levels.

**Temporary transvenous pacing** can be used to treat refractory TdP. Temporary pacing is used based on the fact that the QT interval shortens with a faster heart rate. Therefore, pacing can be effective in terminating torsade. Atrial pacing is the preferred mode because it preserves the atrial contribution to ventricular filling and also results in a narrower QRS complex and hence a shorter QT. Pacing should be instituted at a rate of 90–110 bpm until the QT interval is normalized. Overdrive pacing may be necessary at a rate of up to 140 bpm to control the rhythm.

**Patients who are in extremis** with TdP, or who develop ventricular fibrillation, should be treated with
**electrical cardioversion or defibrillation.**

All arrhythmias are adverse events and must be recorded on the appropriate form in the CRF.

Patients who have arrhythmias should be reviewed by a cardiologist.

Fluconazole should be restarted when the arrhythmia is resolved for 24 hours. Tamoxifen will not be restarted for any patient who has a ventricular tachyarrhythmia.

### Syncope

Any patient who has sudden onset of loss of consciousness will be assessed by a clinician according to normal practice. ECG and electrolytes will be checked and corrected. The patient will be monitored in a high care environment. Tamoxifen administration will be stopped and not restarted. Patients who have syncope due to suspected arrhythmia should be reviewed by a cardiologist.

## Stopping study drug

Occasionally it can be necessary to stop the study intervention (Tamoxifen). Stopping a patient’s treatment does not mean that they have withdrawn from the study. Patients continue in the study and follow the protocol schedule for visits and investigations until its conclusion.

### Indications for stopping Tamoxifen

Tamoxifen is generally a well tolerated drug. Studies from breast cancer suggest increased risks of pulmonary embolism, and uterine malignancies, but the absolute risks of these are very low and they are associated with prolonged use over many months rather than short course duration, as will be used in this study
^29^. It is unlikely that the 2 weeks duration of treatment in this study will increase these risks. Prolongation of the QTc interval is to be expected in this study and does not necessarily indicate a risk of ventricular arrhythmia. The management of study drug in the face of prolonged QTc (>500ms) has been described in section ‘Management of Adverse Events’, subsection ‘Prolonged QTc’. However, Tamoxifen will be stopped and not restarted if any of the following events occur in a particular patient:

1. deep venous thrombosis2. venous thromboembolism3. syncope4. ventricular tachyarrhythmia

## Withdrawal from the trial

Patients may voluntarily withdraw from the trial for any reason. If this occurs, the patient will be referred to standard clinical care facilities. The patient’s withdrawal from the trial will not affect their access to the best standard of care within the local health system. With the agreement of the patient, clinical and laboratory assessment should be performed and recorded at the time of withdrawal. Patients may also decide to stop study treatment without withdrawing from the study, in which case Tamoxifen will be stopped and follow-up will continue as per the study schedule.

## Adverse events

### Definition of adverse events

An adverse event (AE) is any undesirable event that occurs to a study participant during the course of the study whether or not that event is considered related to the study drug. An AE can, therefore, be any unfavorable and unintended sign (including an abnormal laboratory finding, for example), symptom, or disease temporally associated with the study drug, whether or not considered related to the study drug.

Examples include:

An increase in severity (grade) or frequency of a pre-existing abnormality or disorder (events that are marked by a change from the participant’s baseline/entry status, including changes in blood tests such as electrolytes)All reactions from sensitivity or toxicity to study drugInjuries or accidents (e.g., for a fall secondary to dizziness, “dizziness” is the event and the injury secondary to the fall is the “outcome”)New clinically significant abnormalities in clinical laboratory values, physiological testing or physical examination.

Stable chronic conditions, such as arthritis, which are present prior to clinical trial entry and
do not worsen are not considered AEs and will be documented in the subject’s clinical chart as medical history. 

Clinical or laboratory events are considered adverse events only if they occur after the first dose of study treatment and before the patient completes trial participation. (See below for reporting of adverse events.)

### Definition of Serious Adverse Events

An AE is considered to be "serious" if it results in one of the following outcomes

Death,Life-threatening event (the subject was at immediate risk of death at the time of the event; it does not refer to an event which hypothetically might have caused death if it were more severe),Inpatient hospitalization or prolongation of existing hospitalizationPersistent or significant disability/incapacity (a substantial disruption of a person's ability to conduct normal life functions),Congenital anomaly/birth defectImportant medical event that may not be immediately life-threatening or result in death or hospitalization but may jeopardize the patient or may require intervention to prevent one of the other outcomes listed in the definition above.

### Definition of Unexpected Serious Adverse Events

Unexpected Serious Adverse Events are untoward medical events which fit one or more of the criteria for SAEs above and which are not considered a part of normal clinical progression of disease or an expected drug reaction. Any event which becomes of concern to the investigators or study doctors during the course of the trial may be reported as a USAE.

### Assessment of Adverse Events

Adverse events will be defined according to the
Common Terminology Criteria for Adverse Events (CTCAE). New AIDS defining events will be defined according to the revised CDC criteria modified for this trial (see extended data, Appendix 3
^58^). In the event that an adverse event is not described within the CTCAE definitions, or is a new AIDS defining event, the following generic severity grading will be used: 

**Grade 1 Mild;** asymptomatic or mild symptoms; clinical or diagnostic observations only; intervention not indicated.

**Grade 2 Moderate;** minimal, local or noninvasive intervention indicated; limiting age-appropriate instrumental Activities of Daily Living (ADL)*.

**Grade 3 Severe or medically significant but not immediately life-threatening;** hospitalization or prolongation of hospitalization indicated; disabling; limiting self-care ADL**.

**Grade 4 Life-threatening consequences**; urgent intervention indicated.

*Instrumental ADL refer to preparing meals, shopping for groceries or clothes, using the telephone, managing money, etc.

**Self-care ADL refer to bathing, dressing and undressing, feeding self, using the toilet, taking medications, and not bedridden.

 [Note: “Life-threatening” as a severity grade is not necessarily the same as “life-threatening” as a “serious” criterion used to define a serious adverse event. The former is a “potential” threat to life and the latter is an “immediate” threat to life.]

A
**laboratory abnormality** only needs to be recorded as a clinical adverse event if it is associated with an intervention. Intervention includes, but is not limited to, discontinuation of a current treatment, dose reduction/delay of a current treatment, or initiation of a specific treatment. In addition, any medically important laboratory abnormality may be reported as an adverse event at the discretion of the investigator. This would include a laboratory result for which there is no intervention but the abnormal value suggests a disease or organ toxicity. Laboratory events will be graded according to CTCAE definitions.

If clinical sequelae are associated with a laboratory abnormality, the diagnosis or medical condition should be reported as the adverse event (e.g., renal failure, haematuria, cardiac arrhythmia) - not the laboratory abnormality (e.g., elevated creatinine, urine RBC increase).

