### Secondary endpoints

***Survival until 10 weeks after randomization.*** International treatment guidelines recommend 10 weeks of high dose antifungal therapy for cryptococcal meningitis – an initial phase of amphotericin based induction therapy for 2 weeks followed by 8 weeks of moderate to high dose fluconazole. The rate of survival until this 10 week period of therapy is completed is a frequent endpoint in trials of treatment for cryptococcal meningitis
^8,
9,
44^. Improvements in EFA over the first 2 weeks of treatment have been associated with improved survival at 10 weeks. Therefore survival until 10 weeks after randomization will be a secondary endpoint in this study.

***Disability at 10 weeks.*** Disability is an expected consequence of cryptococcal meningitis, including blindness, deafness and other focal neurological deficits. In addition to improving the sterilizing power of antifungal therapy, Tamoxifen may also reduce the rates of disability in survivors. Neurological disability will be assessed using the modified Rankin score and the Two Simple Questions and classified as good, intermediate, severe disability, or death, as previously described
^45^.

***Adverse events.*** The proportion of patients with any grade 3 or 4 adverse event, serious adverse event, or unexpected serious adverse event will be compared between treatment groups.

***Rate of IRIS until 10 weeks (in HIV infected patients only).*** We will model the rate of IRIS over time with a cause-specific hazards model taking into account the competing risk of prior death. CM-related IRIS will be defined as per the recent proposed definition
^46^.

***Rate of Cryptococcal meningitis relapse.*** A pragmatic definition of relapse will be used. This is defined as either intensification of antifungal therapy above that according to the study antifungal schedule, or readmission for treatment of cryptococcal disease.

***QT prolongation.*** Prolongation of the QT interval is a potential side-effect of both Tamoxifen and fluconazole, although it is not clear that either drug increases the risk of Torsade de Pointes, a potentially life-threatening arrhythmia. The QT interval will be estimated manually from 3 chest and 3 limb leads from a high resolution (50mm/sec) 12-lead ECG. The median value will be determined and used to calculate the corrected QT interval (QTc) using Framinghams’ formula.

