### Adverse events.

The frequency of serious and grade 3 & 4 adverse reactions as well as the frequency of specific adverse events will be summarized (both in terms of the total number of events as well as the number of patients with at least one event). The proportion of patients with at least one such event (overall and for each specific event separately) will be summarized and (informally) compared between the two treatment groups based on Fisher’s exact test.

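### Recording of laboratory abnormalities is mandatory only when someone intervenes, so the laboratory part of this open-label adverse event comparison is at risk of arm-dependent recording

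*Protocol article*

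**What the plan says.** Assessment of Adverse Events states that a laboratory abnormality "only needs to be recorded as a clinical adverse event if it is associated with an intervention". Interventions include "discontinuation of a current treatment, dose reduction/delay of a current treatment, or initiation of a specific treatment". The same paragraph adds an optional route: "any medically important laboratory abnormality may be reported as an adverse event at the discretion of the investigator", which covers "a laboratory result for which there is no intervention but the abnormal value suggests a disease or organ toxicity". If a laboratory abnormality has clinical sequelae, "the diagnosis or medical condition should be reported as the adverse event".

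Definition of adverse events, by contrast, gives new laboratory abnormalities of clinical significance as an example of an adverse event and does not require that anyone acted. Adverse event recording limits what is entered to grades 3 and 4.

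The endpoint under Secondary endpoints is "The proportion of patients with any grade 3 or 4 adverse event, serious adverse event, or unexpected serious adverse event". The matching analysis section says: "The frequency of serious and grade 3 & 4 adverse reactions as well as the frequency of specific adverse events will be summarized". It then compares the proportions of patients with at least one such event, informally, by Fisher's exact test.

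**The concern.** Whether an intervention takes place is a decision made at the bedside, and in an open-label trial it can be made knowing the arm. A recording rule tied to that decision can produce different counts from identical laboratory values. One of the listed interventions, delaying or stopping a current treatment, includes withholding tamoxifen, which control patients do not receive.

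Electrolyte disturbance is described in the protocol as common and bears on the QT question, so laboratory events may form a sizeable share of the grade 3–4 counts. Those counts feed the secondary aim of showing that tamoxifen can be given safely, the DSMB report by arm, and the decision on a larger trial. A difference produced by recording could be read as toxicity.

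The analysis text also uses *reactions* where the endpoint uses *events*. That leaves unclear which events the overall summary covers.

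**Working it through.** The plan gives no figure for this point, so there is nothing to reproduce. The check compares the passages and then illustrates the possible size.

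**1. The two definitions.** Definition of adverse events counts a clinically significant laboratory abnormality without any condition. Assessment of Adverse Events makes recording obligatory only with an intervention and otherwise optional. A grade 3 potassium value on which nobody acts is an adverse event under the one and need not be recorded under the other.

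**2. Which interventions differ by arm.**
- *Tamoxifen arm only:* omitting tamoxifen under Prolonged QTc, including step 5c, where potassium, magnesium or calcium is abnormal at grade 2 or above. Step 5 also ties the repeat electrolytes to the next due tamoxifen dose, a time point that controls lack.
- *Not limited by arm:* the instruction in step 4, "Correct abnormal electrolytes into the mid normal range with intravenous supplementation"; the electrolyte monitoring and correction promised for all patients under Prolongation of the QT interval; the laboratory schedule under Blood; and the pre-emptive replacement and creatinine rule for amphotericin under Electrolyte disturbances and raised creatinine.

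A tamoxifen patient therefore has one extra route to mandatory recording. Starting replacement is itself an intervention and is open to both arms, so in many patients the extra route would add nothing to a count of patients with at least one event.

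**3. Illustration of size.** The input from the protocol is 25 patients per arm. The true rate *p* (equal in both arms) and the recording probabilities *r*T (tamoxifen) and *r*C (control) are assumptions; the protocol gives none. The apparent rates are *p* × *r*T and *p* × *r*C, so the spurious difference is *p* × (*r*T − *r*C). The chance that Fisher's exact test gives p < 0.05 (two-sided) comes from exact enumeration of both binomials.

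| *r*T v *r*C | *p* = 20% | *p* = 40% | *p* = 60% | *p* = 80% |
|---|---|---|---|---|
| 100% v 100% | 0 points; 2.22% | 0; 2.95% | 0; 2.95% | 0; 2.22% |
| 95% v 90% | 1 point; 2.24% | 2; 2.91% | 3; 3.57% | 4; 2.85% |
| 100% v 80% | 4 points; 3.03% | 8; 5.42% | 12; 9.96% | 16; 14.96% |
| 95% v 70% | 5 points; 3.50% | 10; 6.80% | 15; 14.20% | 20; 22.83% |
| 95% v 50% | 9 points; 7.12% | 18; 18.75% | 27; 41.71% | 36; 68.29% |

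For example, with *p* = 40% and 95% v 70%: 0.40 × (0.95 − 0.70) = 0.10, or 10 points. Equal but incomplete recording (80% v 80% or 50% v 50%) gives no spurious difference. The bias arises only from a gap between arms, and it matters only if the gap is large.

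**4. Events and reactions.** The endpoint is defined on events. The analysis sentence begins with *reactions*, continues with specific adverse *events*, and the next sentence tests patients with at least one such *event*. No step is described by which an event would be classed as a reaction.

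**5. What does not depend on the rule.** Survival is analysed by Cox regression. QTc is analysed from measured values, by category and by maximum change. Neither passes through laboratory adverse event recording.

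**The case against.** The strongest reply is that the gap in recording is probably small. Monitoring and correction of electrolytes are promised to everyone, and starting correction already makes recording mandatory in either arm. The QTc pathway is entered because QTc exceeds 500 ms, not because of an electrolyte value, and its recheck and correction steps are not limited to tamoxifen patients. Extra correction towards mid-normal values would mostly concern low grades, which are not recorded. The investigator may report abnormalities without an intervention, and clinical sequelae are reported in any case. The Fisher comparison is declared informal, and nothing prevents a table of graded laboratory values in an analysis plan that is not shown here. Most of this stands, and it limits the size of the concern. It does not remove it: the discretionary route is optional and unblinded, and the protocol describes no comparison of laboratory abnormalities that is free of the recording rule.

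A reader might infer three stronger things, none of which the document supports:
- *The whole safety comparison reflects staff behaviour by arm.* The risk is confined to laboratory-based adverse events.
- *The same electrolyte value will lead to action more often on tamoxifen, by a large margin.* Recording of 90% v 60%, for instance, would turn 10 true events per arm into 9 v 6 (10 × 0.9 and 10 × 0.6). That supposes 4 of 10 affected controls go without recorded action, against the stated intention to correct disturbances in all patients. Even then Fisher's test gives p = 0.54.
- *The word* reactions *imposes a causality filter.* The surrounding sentences speak of events, and adverse events are defined regardless of relation to the drug. It reads as a wording inconsistency.

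**Conclusion.** The concern holds as a risk of arm-dependent recording in one part of the safety analysis. It rests on three features of the text: mandatory recording tied to an intervention, open-label treatment, and one qualifying intervention available in only one arm. The mismatch between the two adverse event sections adds to it.

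The size cannot be determined from the protocol. It is negligible if recording is nearly complete in both arms and becomes material only with a recording gap for which the document gives no evidence. The calculations are illustrations under assumed rates, not estimates. This is an improvement worth making because it is cheap; it does not undermine the trial's safety evidence.

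**What to change.** Enrolment is complete and analysis is under way according to Trial status, so recording cannot be changed, but the analysis can.

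1. For the between-arm comparison of laboratory abnormalities, take the values from the scheduled tests common to both arms, grade them by CTCAE, and count patients with a grade 3–4 value whether or not anyone intervened. Leave unscheduled retests out of that comparison, because extra testing tied to tamoxifen doses would give one arm more chances to show an abnormal value.
2. Keep the recorded adverse events as a separate descriptive table, and state there that laboratory events entered it under the intervention rule.
3. In the adverse events analysis section, replace *adverse reactions* with *adverse events*, to match the endpoint.
4. Reconcile the treatment of laboratory abnormalities in Definition of adverse events and Assessment of Adverse Events.

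The set of scheduled tests should be fixed first: as printed, Table 2 shows no creatinine on days 5 and 9, while the Blood section lists those days. The cost is minor programming on data already collected, one changed word and one reconciled definition. Event counts will rise in both arms. The change removes dependence on recording; it does not remove any effect that different correction may have had on the values themselves.
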